### Infant

Healthy term newborns will be recruited into the study. Details of inclusion and exclusion criteria are as follows:

#### Inclusion

Healthy, term infant as determined by medical history, physical examination, and judgment of the study physician.

Weight of 2.5 kg or greater at the time of enrolment.

#### Exclusion

Previous vaccination with any EPI vaccine

Major known congenital malformation

Apgar score <8 at 5th min.

Physician assessment of potential high-risk infant including significant risk factors for sepsis/morbidity (such as maternal symptoms suggestive of urinary tract infection in the peri-partal period), or macrosomia (birth weight above 4 kilograms).

## Randomization and Blinding

Following assessment of eligibility by the study physician, newborns will be randomly assigned to 1 of 12 groups in The Gambia (60 per group), and 1 of 4 groups in PNG (20 per group), using a computer-generated block randomization sequence. In The Gambia, the code will allow block randomization of 720 study participants into 12 groups, using random block sizes of 24 and 48. In PNG, block sizes of 8 will be used. Each study participant will be assigned sequential identification numbers (IDs) starting from 001 to 720 for The Gambia, and 1,001–1,080 in PNG. A check digit character will be augmented to each of these numbers to make up the participant IDs which will be generated using the Damm algorithm (https://en.wikipedia.org/wiki/Damm_algorithm; date accessed 08 November 2016). Here the check digit numbers 0–9 will be converted to letters A-H and J-K. The IDs for the Gambian cohort will be prefixed with the letter “G” which stands for Gambia. The randomization code will use the web application developed by the Statistics and Bioinformatics department at MRCG to generate the IDs including the check digit and prefix as detailed above (the app is available on https://stats.mrc.gm/chkdgt-id/). Randomization code for the PNG cohort will be generated at BCH using similar methods. Randomization groups will be printed on cards labeled with the participant identification number and allocated in the sequence in which the infants will be recruited. Cards will be sequentially allocated by clinical staff as participants are screened.

Due to the nature of randomized groups and difficulty of blinding to randomized vaccine groups, staff in direct contact with participants will be unblinded, while all laboratory staff at the sites will be blinded to participants assigned group throughout the study.

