## Participant Selection

### Study Sites

In the Gambia, 720 mother-infant pairs (60 per group) will be recruited through delivery rooms at one secondary level care institution; The Kanifing General Hospital and one primary health facility; The Banjullinding Health Center in The Gambia. In PNG, 80 mother-infant pairs will be recruited at Goroka Hospital, the only tertiary hospital in the Eastern Highland Province of PNG. Maternal infant pairs will be recruited within the first 24 h of the infants' life.

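### Papua New Guinea cohort: one fixed block size of 8 for four open arms lets recruiting staff who know or infer it deduce some assignments in advance; varying, undisclosed sizes are a cheap improvement

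*Protocol article*

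**What the plan says.** All of this is in the Protocol article.

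- **Arms and numbers.** Under Randomization and Blinding, infants are assigned to "1 of 4 groups in PNG (20 per group"). Study Sites gives one centre: "In PNG, 80 mother-infant pairs will be recruited at Goroka Hospital". According to the Abstract the four arms are hepatitis B vaccine (HepB) alone, BCG alone, both, and both delayed.
- **Blocks.** For PNG: "In PNG, block sizes of 8 will be used". For The Gambia, with 12 groups and 720 infants, the list is made "using random block sizes of 24 and 48". The PNG code is generated at Boston Children's Hospital (BCH) by methods described as similar. That phrase does not turn the one stated size into a random one.
- **Allocation.** PNG identification numbers run in sequence from 1,001 to 1,080. The assigned group stands on a card that bears the infant's number, and the cards follow the order of recruitment. On who hands them out, the section says: "Cards will be sequentially allocated by clinical staff as participants are screened".
- **Blinding.** "staff in direct contact with participants will be unblinded"; site laboratory staff are blinded.
- **Eligibility.** It is assessed before assignment. The infant criteria include the study physician's judgment of health (Inclusion) and "Physician assessment of potential high-risk infant including significant risk factors for sepsis/morbidity" (Exclusion). Others are fixed limits, such as weight and Apgar score.
- **Timing.** Study Design places PNG after completion and analysis of the Gambian study.

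**The concern.** With four arms in blocks of 8, every eight consecutive infants contain exactly two per arm. Recruiting staff see each assignment as it is made. Numbering is sequential at one hospital, so anyone who knows the size also knows where each block ends (1,008, 1,016 and so on). The remaining assignments in a block narrow as it fills, and the last is always determined.

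Assessing eligibility before drawing a card protects against selection only if the next card cannot be foreseen. Some criteria leave room for judgment. A physician who knows that the next infant will, or cannot, enter the delayed arm could apply them differently. The section on Risks and Benefits itself ties careful screening to the safety of infants in that arm. It also makes the arm the comparator that separates normal first-week immune development from vaccine-induced change. At stake is the comparability at entry of four arms of 20 infants in the cohort meant to validate the Gambian signatures.

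**Working it through.** **Inputs** (Randomization and Blinding; Study Sites): 4 arms × 20 = 80 infants; block size 8; 80/8 = 10 complete blocks; 8/4 = 2 places per arm per block. The stated totals are consistent. One assumption comes from outside the text: the observer knows the block size and every past assignment.

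**1. Assignments known with certainty.** The 8th is always determined. The 7th is determined only when the last two places belong to the same arm. Given one of them, 1 of the other 7 places in the block is of that arm, so the probability is 1/7. Earlier ones are never determined, because three or more remaining places cannot all belong to one arm.

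Per block: 1 + 1/7 = 8/7 = 1.143. Share: 1.143/8 = 14.3%. Over ten blocks: 11.4 of 80, and never fewer than 10.

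**2. Delayed arm already used up.** After k assignments, both delayed places are gone with probability k(k−1)/(8×7). Summing over k = 0 to 7: (0+0+2+6+12+20+30+42)/56 = 112/56 = 2 per block, which is 25%, or 20 of 80.

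**3. HepB-at-birth status known.** Two arms give HepB at birth (4 places) and two do not (4 places). The expected number of places left once one kind has run out is 4/5 + 4/5 = 1.6 per block, which is 20%, or 16 of 80.

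**4. Best-guess success.** The guess is always the arm with most places left.

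| Position | Probability correct |
|---|---|
| 1 | 2/8 = 0.250 |
| 2 | 2/7 = 0.286 |
| 3 | 2/6 = 0.333 |
| 4 | 2/5 = 0.400 |
| 5 | (16/70)(1/4) + (54/70)(2/4) = 0.443 |
| 6 | (32/56)(1/3) + (24/56)(2/3) = 0.476 |
| 7 | (1/7)(1) + (6/7)(1/2) = 0.571 |
| 8 | 1.000 |

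At position 5, 16/70 is the chance that the four remaining places are all of different arms (2⁴ of C(8,4) = 70). At position 6, 32/56 is the same for three places (4 × 2³ of C(8,3) = 56). The sum is 3.76 of 8 = 47.0%, against 25% by chance.

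**5. The Gambian list for comparison.** With 12 groups, sizes 24 and 48 chosen at random, and a guesser who knows the two sizes but not which is in use, simulation gives about 9.8 of 720 certain (1.4%). The best guess is right about 20% of the time, against 1/12 = 8.3% by chance.

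**6. Varying sizes in PNG.** The sizes below are my examples, since the article names none. The guesser knows the menu of sizes and the total of 80, but not the size in use. Results are simulated.

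| | Fixed 8 | 8/12/16, total 80 |
|---|---|---|
| Known with certainty | 14.3% | about 3% to 4% |
| Delayed arm ruled out | 25% | about 6% to 7% |
| HepB-at-birth status known | 20% | about 4% to 5% |
| Best guess correct | 47% | about 44% to 45% |

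The ranges reflect separate simulations; the exact figure depends on how the total of 80 is enforced. Certain knowledge falls by roughly a factor of four, while the best-guess rate hardly moves. A menu that includes very small blocks can be worse on that measure: sizes 4 and 8, without the constraint on the total, give 48.4%.

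**The case against.** **Staff may not know the size.** The list is made off site. The article does not say that recruiting staff are told the block size, nor that it is withheld. Handling of this kind is often left to a full protocol or to written procedures, which are not shown. This stands as a condition on every figure above. It does not remove the point: the article prints the size, and with open arms and ten equal blocks in one running sequence it can be inferred.

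**Room for steering is limited.** Weight, Apgar score and the maternal rapid tests are fixed criteria, and enrolment must occur within 24 hours of birth. The study was judged to pose minimal risk, which weakens the motive. All of this stands, but physician judgment remains among the criteria.

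**The damage would be partly visible.** Every infant has a baseline sample, so an imbalance in baseline profiles could be seen and examined within infant. Blinded laboratories protect the measurements. Both points stand. Neither restores comparability at entry on traits that the baseline sample does not capture.

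**Small blocks are conventional, and the change has a price.** Blocks of 8 fit evenly into batches of 24 or 48 participants (Laboratory Quality Control Measures); blocks of 12 and 16 fit less neatly. The Gambian sizes may have been chosen to match those batches, since the article does not say that concealment was the reason. This also stands.

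A reader might go further and infer that PNG staff do foresee assignments, that the cards are left unsealed, or that a few steered infants could create or hide a between-arm signature. The documents support none of these. They do not describe how the cards are concealed, they give no figure for steering, and no calculation links a number of steered infants to a false or missed signature.

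**Conclusion.** The point holds as a conditional weakness of the PNG randomization. The article fixes one small block size for four open arms at one hospital. If recruiting staff know or infer it, 14.3% of assignments are certain in advance, the delayed arm is excluded for 25%, HepB-at-birth status is known for 20%, and a best guess succeeds 47% of the time. These shares describe what could be foreseen, not how much bias would follow; the number of infants steered cannot be obtained from the document.

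The exposure is selection at entry in an 80-infant validation cohort. It is not biased measurement, and it does not reach the 720-infant Gambian core study. I rate it a cheap improvement of minor to moderate weight.

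**What to change.** Replace the sentence "In PNG, block sizes of 8 will be used" with a statement that PNG uses randomly varying block sizes in multiples of 4 (for example 8, 12 and 16), constrained to total 80 so that each arm keeps 20 infants. State that the list is generated at BCH and that the sizes are not disclosed to site staff. Non-disclosure has to be written in, because varying the sizes alone leaves the best-guess rate almost where it was.

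The cost is a short protocol change and one new run of the PNG list. The stated order of the two studies leaves time before PNG recruitment. Balance between arms at intermediate points becomes slightly looser. PNG assay batches need a little more planning, because blocks of 12 or 16 will not always fill batches of 24 or 48 participants evenly.

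### One unstratified card sequence serves two Gambian facilities of different care level, which leaves avoidable chance imbalance by facility across the 12 groups

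*Protocol article*

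**What the plan says.** Study Sites in the protocol article states that Gambian pairs "will be recruited through delivery rooms at one secondary level care institution; The Kanifing General Hospital and one primary health facility; The Banjullinding Health Center", 60 per group, within 24 hours of birth. Papua New Guinea has one hospital, so the point concerns The Gambia only.

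Randomization and Blinding describes one list: "the code will allow block randomization of 720 study participants into 12 groups, using random block sizes of 24 and 48". There is one ID run: "Each study participant will be assigned sequential identification numbers (IDs) starting from 001 to 720 for The Gambia". The letter prefix marks the country, and no facility prefix or ID range is given. Cards carry the ID and the group, are "allocated in the sequence in which the infants will be recruited", and are handed out by staff: "Cards will be sequentially allocated by clinical staff as participants are screened". No facility stratum is stated.

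Laboratory Quality Control Measures ties the OMIC batches to the randomization blocks. A batch holds 24 to 48 participants, and the 12 sub-groups are equally represented in it. Facility is not mentioned there.

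**The concern.** A secondary hospital and a primary health centre may differ in the mothers they serve, in the delivery setting and in the time a sample takes to reach the laboratory, for which the article allows up to 4 hours. Facility could therefore move both OMIC features and antibody titre. The list keeps the 12 groups equal in size overall, but it does nothing to equalise them within the hospital or within the health centre.

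Two analyses are affected in different ways. Comparisons between randomized groups carry whatever facility imbalance chance produces, and with only 60 infants per group this can be noticeable. Associations between features and titre, which are the main aim in the Study Analysis Plan section, are not protected by randomization at all. If facility affects both variables, it can produce an association by itself.

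**Working it through.** **1. The plan's own figures.** 12 × 60 = 720. Each block gives 24/12 = 2 or 48/12 = 4 infants per group. With a blocks of 24 and b blocks of 48, a + 2b = 30 fills 720 exactly. The stated structure is consistent.

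**2. Input not in the documents.** The split between facilities is not given. I assume that the larger facility supplies p = 50%, 70% or 80%, with 90% as an extreme.

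**3. Rough size by formula.** With facility unrelated to position in the list, the number from the larger facility in a group of 60 has SD of about √(60·p·(1−p)): 3.9, 3.5 and 3.1 infants at 50, 70 and 80%. The SD of the difference in share between two groups of 60 is √(2p(1−p)/60) = 9.1, 8.4 and 7.3 points. Between two arms of 180 it is √(2p(1−p)/180) = 5.3, 4.8 and 4.2 points.

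**4. Simulation.** 3,000 runs per scenario, with 720 infants and random blocks of 24 and 48. One list was compared with a separate list per facility. Entries are the average highest-minus-lowest gap in facility share, in percentage points, with the 95th percentile in brackets.

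| Larger facility's share (assumed) | One list, 12 groups | One list, 4 arms | Two lists, 12 groups | Two lists, 4 arms |
|---|---|---|---|---|
| 50% | 21 (30) | 8 (13) | 3 (4) | 1 (2) |
| 70% | 19 (27) | 7 (12) | 3 (5) | 1 (2) |
| 80% | 17 (23) | 6 (11) | 3 (5) | 1 (2) |
| 90% | 13 (18) | 5 (8) | 3 (6) | 1 (3) |

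These are extremes over all groups. For any two given groups of 60 under one list, the mean gap is only 4 to 7 points.

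**5. Effect on a between-group contrast (illustration).** Suppose that facility explains 10% of the variance of an outcome and the split is 50/50. The facility difference is then √(0.10/0.25) = 0.63 SD.
- Four arms: an 8-point gap shifts the contrast by 0.08 × 0.63 = 0.05 SD. The standard error is √(2/180) = 0.105 SD.
- Twelve groups: a 20-point gap shifts it by 0.20 × 0.63 = 0.13 SD. The standard error is √(2/60) = 0.18 SD.

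**6. Effect on a feature-titre association (illustration).** Suppose that facility explains 10% of the variance of both variables, acting in the same direction, and they are otherwise unrelated. The induced correlation is √0.10 × √0.10 = 0.10. Within one vaccine schedule, n = 3 × 60 = 180, and the Fisher z shift is atanh(0.10) × √177 = 0.1003 × 13.30 = 1.33. The chance of p < 0.05 is Φ(1.33 − 1.96) + Φ(−1.33 − 1.96), about 27%. At a 5% share, r = 0.05, the shift is 0.67 and the chance is about 10%. Stratifying the list does not alter these figures.

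**The case against.** Unstratified blocked randomization is valid. Facility is balanced in expectation, and the usual type I error already allows for chance imbalance. The largest gap among 12 groups is the least flattering summary. For the four arms the shift in step 5 is about half a standard error even under a generous facility effect. All of this stands, and it limits the point to balance and precision.

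A reader might infer that a single deck of cards cannot serve two delivery rooms, so that the procedure cannot be carried out. The documents do not support this. One sequence works if the next card is held or released centrally, or if one team recruits at one facility at a time. The article neither states nor excludes either. Custody of the cards is also the kind of detail left to the full protocol or to the written procedures promised under Quality Control and Quality Assurance.

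A reader might also take the 27% in step 6 as the harm done by the single list. It is not. It rests on an assumed facility effect that no document reports, and eligibility is narrow (healthy term infants, vaginal delivery, restricted birth weight), which makes a large effect harder to presume. It would be the same under stratified lists. Nothing in the article rules out adjustment, and the choice of model terms may properly sit in an analysis plan that is not shown, so the lack of a facility term in the article is not itself a fault.

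Facility-specific blocks have a drawback: because OMIC batches follow the blocks, batch could become tied to facility. This is a fair objection, and the change has to deal with it.

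**Conclusion.** The point holds as a design improvement and not as an error that invalidates the trial. The article fixes one unstratified sequence for two facilities of different care level. On an assumed share of 50% to 80% for the larger facility, this leaves an average highest-lowest gap of about 17 to 21 points across the 12 groups and 6 to 8 points across the four arms, against about 3 and 1 points with facility-specific blocks. The imbalance is modest for the arms. It is more noticeable for the groups of 60, which carry the comparisons specific to a sampling day.

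The size of any facility effect on features or titre is undocumented, so no actual false-positive rate can be claimed. The 27% and 10% figures show only what effects of 10% and 5% would do if facility were ignored in the analysis.

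**What to change.** In Randomization and Blinding, replace the single list by two blocked lists, one per facility, each with its own reserved ID range and the block sizes already chosen. Include facility as a term in the between-group models and in the feature-titre models. The two parts do different work: the lists improve balance between groups, while the model term addresses confounding of feature-titre associations.

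The cost is a rerun of the list generator and a short amendment. The total stays at 720. Group totals may depart from 60 by a few infants if a facility stops mid-block.

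Laboratory batches should combine infants from both facilities, for example one 24-infant block from each in a 48-participant batch, which stays within the stated batch size. A 48-infant block would be divided into two sets of 24 with 2 per group. If recruitment is uneven, not every batch can be mixed this way. At an 80% share the smaller facility supplies 0.2 × 720 = 144 infants, or 144/24 = 6 blocks, for 720/48 = 15 batches. Its blocks should then be spread over the recruitment period, so that batch and facility can still be told apart.

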## Study Procedures

### Cohort Overview

The cohort overview is detailed in Table 1.

#### Screening

Following the informed consent signature and pre-test counseling, a detailed medical and pregnancy history will be obtained from each eligible woman. Women will be screened for Human Immunodeficiency Virus (HIV)-I and -II and HB-sAg using rapid diagnostic tests. Individuals positive for any of these antigens will be excluded from the study, offered post-test counseling and referred for care as appropriate. It will be essential to exclude HB-sAg positive mothers to ensure that infants born to these mothers receive HepB vaccine at birth to minimize transmission risk as recommended by the World Health Organization (WHO). The study team will ensure receipt of this vaccine within 24 h of life for all infants whose mothers tested positive for HepB, but these infants will remain excluded from further study procedures. Similarly, infants born to HIV-positive mothers will be excluded and referred for further management. Inclusion of HIV-exposed or positive infants could impact on the biological signatures. Each newborn infant will then undergo a full newborn exam to rule out obvious congenital anomalies and other signs of ill health.

#### Enrolment

Eligible mother-infant pairs will be randomized to one of 12 or 4 groups in The Gambia and PNG cohorts, respectively, and study procedures carried out as detailed below.

#### Follow-Up

The mother's participation will end following this initial visit while the infant will be followed up longitudinally over a 5-months period as dictated by the study design detailed in Table 1.

#### Termination

Participation in the study will be completed 1 month after the primary infant series vaccination, corresponding to 1-month post the 4th dose of HepB vaccine, or following the week one follow-up visit for infants in the delayed vaccine group (Groups 10 to 12) in The Gambia. Participation in PNG will be complete after the second visit for PNG; Table 1).

#### Early Termination

Infants will exit the study prior to the above if consent is withdrawn; the study team can no longer reach the participant's caregiver and/or caregiver does not present for a visit at the clinic (lost to follow-up); the participant moves out of the study area; or the infant dies.

#### Discontinuation Criteria

Study participation could also be discontinued for individual participants if in the judgement of the investigator participation poses an additional risk to the participant other than the already anticipated minimal risk. The study could also be discontinued following assessment by the Ethics Committee that the study posed significant unacceptable risk to the participants based on safety signals.

#### Strategies to Enhance Retention

To enhance participant retention and adherence to follow-up schedule, a field calendar will be set up which automatically generates the follow-up schedule in REDCap [a browser-based, metadata-driven electronic data capture (EDC) software and workflow methodology for designing clinical and translational research databases (https://www.project-redcap.org)], following enrolment. Each participant will be assigned to a field worker on the day of enrolment. This individual will keep a record of the follow-up schedule in their logbook. In addition, daily follow-up calendars will be printed from REDCap by field supervisors to ensure a double check for follow-ups. As an additional check, the clinician will maintain a field diary on which visits can checked off as they occur. The responsible field worker will call the participant to remind him/her of the scheduled visit at least 24 h prior to the visit (first week of life visit) or the weekend prior to the scheduled visit and again 24 h prior to the visit (subsequent visits). Participants will be picked up by a study vehicle for the first week of life visits to ease logistics during a time when mother and infant will be recovering from the birth process. Participants will be encouraged to share travel plans with the responsible field worker as soon as possible to allow for rescheduling of visits.

